#### Sleep scheduling and sleep restriction

To help participants to reshape sleep patterns to correspond with their individual sleep needs. The participant is helped to reestablish a consistent sleep-wake schedule.

Define individual sleep requirements.Develop a good pre-sleep routineEstablish a strong bed-sleep connectionEliminate wakefulness from bed (rising if not asleep within around 20 to 30 minutes)Establish and follow a regular and consistent night-to-night sleep schedule, go to sleep in the same bed at the same time each night, and arise immediately on awakening at the same time each morningIncrease sleep efficiency through scheduling sleep in relation to current total sleep; restrict participants’ allowed time in bed to the actual sleeping time according to the participants’ sleep diary. Adjust the time-in-bed period as sleep efficiency improves from week to week. Participants are instructed to get up at a regular time, even if they did not have enough sleep the night beforeAvoid daytime napsAvoid recovery sleep as compensationEncourage and support people in changing their sleep routines to improve 7-day per week compliance

#### Cognitive therapy

The participant learns about ways to reduce mental alertness, repetitive thoughts and anxiety that interfere with sleep:

Identify thought patterns and content that interfere with sleepDevelop accurate beliefs and attitudes about sleep and sleep lossPrepare mentally for bed by putting the day to restLearn thought-distraction and imagery techniquesTeach progressive relaxation techniques; the participant is taught how to recognize and control muscular tension through use of exercise instructionsUse these techniques to combat intrusive thoughtsReduce efforts to control sleep and allow it to happen naturallyEncourage and support people in changing their mental approach and to maintain behavior and cognitive changeFurther adjust sleep schedules to maintain sleep efficiency

### Administration of the sleep intervention

Participants receive six weekly sessions delivered by an animated “virtual therapist” (The Prof). These sessions are self-delivered at a convenient time for each participant, over an 8-week period. The program comprises a fully automated media-rich web application, driven dynamically by baseline, adherence, performance, and progress data. At the start of each session, the Prof conducts a progress review with the participant, explores the diary data submitted during the week, the participant’s current sleep status and pattern, and progress achieved against goals previously set. Underlying algorithms feed the delivery of information and provide support and advice in a personally tailored manner. The content of the cognitive behavioral therapy component of the intervention is consistent with the literature, and covers behavioral (for example, sleep restriction, stimulus control) and cognitive (for example, putting the day to rest, thought restructuring, imagery, articulatory suppression, paradoxical intention, mindfulness) strategies, as well as additional relaxation strategies (progressive muscle relaxation and autogenic training) and advice on lifestyle and bedroom factors (sleep hygiene). The intervention is based on a previously validated manual
[24, 27]. Table 
1 summarizes the content and features of the intervention.

**Table 1 Tab1:** **Summary of online sleep intervention**

**Treatment content**	Sleep information/education, sleep hygiene, relaxation, stimulus control, sleep restriction, cognitive techniques (restructuring, paradox, mindfulness, imagery, putting day to rest, thought stopping)
**Duration**	Six sessions over a minimum of 6 weeks
**Delivery context**	Fully online
	Delivered by animated therapist (The Prof)
	No face-to-face contact
**Additional treatment features**	Appointment system, interactive sessions, dynamic feedback against personal goals, progress review at start of each session, automatic calculation of sleep data over time, personal case file, end-of-session quiz, 24/7 access
**Support/motivational system**	Praise/reinforcement contingent on progress, online Wikipedia of sleep-educational topics. Social community of users, moderated by experts. Support/prompts/reminders by Email and mobile SMS ”Graduation ceremony” on course completion

#### Methods to maximize participant adherence to the intervention and follow-up procedures

To improve adherence with follow-up procedures, we schedule follow-up visits at a convenient time for participants and ensure that adequate study staff and an efficient system are in place, to minimize waiting times. Participants access an online daily sleep diary throughout the online sleep intervention, which is completed each morning on rising. Participants are able to set automated mobile text message and/or Email prompts as reminders, to further promote adherence. Members of the Sleepio team also contact participants who are not adhering to the intervention by using standardized Emails and phone follow-up, further to encourage adherence to the intervention.

To reduce losses to follow-up, participants who fail to return for a follow-up visit are contacted by phone and/or mail to arrange an alternative convenient appointment.. The cost of transport to and from the study site is reimbursed on request, further to encourage adherence to the follow-up procedures. If participants are unable to make a final follow-up visit to the study site, a home visit with the participant is arranged, where possible, to obtain final outcome data. If the participant refuses or is unable to attend for any further follow-up visits, we attempt to establish the reason for nonattendance. We believe these measures will help ensure a high adherence rate of >85% and a low loss-to-follow-up rate of <5%, thus maximizing the ability of the trial to detect a true treatment effect.

#### Components of the control intervention

The control intervention consists of advice and education on modifying cardiovascular risk factors and adopting a healthier lifestyle. Specific components include advice on smoking cessation, decreasing alcohol intake, increasing physical activity levels, and adopting a healthy diet. This standardized cardiovascular-risk-factor educational session, which represents usual care, is administered in an identical fashion, to trial participants in both arms.

#### Administration of the control intervention

Specialist nurses with specific training in cardiovascular-risk-factor education (working for Croí), administer the cardiovascular-risk-factor education intervention to participants in groups of one to 15 (current average, six to 10), over a 30–minute period. The control intervention is delivered during week 1 of the trial.

### Follow-up schedule

During the initial visit, all eligible participants who provide written informed consent are randomized. Measurements are carried out on two occasions, at baseline and at the final follow-up visit at 8 weeks.

### Measurements

#### Baseline characteristics and measurement of predictor variables

Data are collected at baseline for relevant participant demographic and clinical characteristics. We use programmed portable monitors to obtain ambulatory blood-pressure readings at 30-minute intervals throughout the whole day, and every 60 minutes at night. We define daytime as the interval from 10 AM to 8 PM, and nighttime as the interval from midnight to 6 AM. These fixed intervals eliminate the transition periods in the morning and evening when blood pressure changes rapidly, resulting in daytime and night-time blood pressure levels that are within 1 to 2 mm Hg of the awake and asleep levels. Within individual subjects, we weigh the means of the ambulatory blood pressure by the interval between readings
[28].

All vascular risk factors are measured in a standardized fashion, consistent with methods used in INTERHEART and INTERSTROKE studies
[29, 30]. Laboratory specimens are collected during baseline and at the 8-week follow-up period. Frozen samples will be analyzed at the GUH laboratory by using standardized storage, handling, and analytic procedures at the end of the trial.

Trained researchers administer the questionnaires (SCI, ISI, PSQI, BDI, and BAI). The data are entered into an electronic case-report form by a trained member of the research team. The following data points are collected:Demographics: date of birth, age, sex, employment statusCo-morbidities: history of diabetes mellitus, atrial fibrillation, dialysis, chronic renal disease, chronic kidney disease, congestive heart failure, dyslipidemia, nocturnal asthma attacks, peripheral vascular disease, current smoker (or smoked within last 6 months), mean number of cigarettes smoked per day, alcohol intake, caffeine intake, and level of physical activityResting heart rateBlood pressure (calibrated, identical machines are used on all participants)Office automated SBP (mm Hg)Office automated DBP (mm Hg)Mean 24-hour ambulatory SBP (mm Hg)Mean 24-hour ambulatory DBP (mm Hg)Daytime peak SBP (mm Hg)Daytime peak DBP (mm Hg)Nighttime peak SBP (mm Hg)Nighttime peak DBP (mm Hg)Mean daytime SBP (mm Hg)Mean daytime DBP (mm Hg)Mean nighttime SBP (mm Hg)Mean nighttime DBP (mm Hg)Current medications: – antihypertensives, statins, other lipid-lowering agents, antithrombotic therapy, oral hypoglycemic agents, insulin, sedatives/hypnotics, and analgesicsSleep questionnaires (PSQI, SCI, ISI)PSQI scorePSQI >5Time in bedSOLWASOTotal sleeping time (TST)Sleep efficiencySCI scoreSCI score ≤5.9ISI scoreISI score ≥15BAI scoreBDI scoreHeight, weight, BMI (calculated by using a standard automated weighing scale and a Leicester height measure)Laboratory measurements (nonfasting samples)Plasma lipoproteins: total cholesterol (TC), low-density lipoprotein cholesterol (LDL-C), high-density lipoprotein cholesterol (HDL-C), triglycerides (TGs), apolipoprotein B (ApoB), and apolipoprotein A1 (ApoA1)Plasma HbA1ceGFR

### Study outcomes

#### Primary efficacy outcome

Change in mean 24-hour ambulatory SBP between baseline and 8 weeks of follow-up. Hypertension has been selected as the primary outcome measure because of its robust association with inadequate sleep and its well-documented association with CVD.

#### Secondary outcomes

Change in mean 24-hour DBP between baseline and 8 weeks of follow-up.Change inDaytime peak SBPDaytime peak DBPNighttime peak SBPNighttime peak DBPMean daytime SBPMean daytime DBPMean nighttime SBPMean nighttime DBPChange in BMIChange in plasma lipoproteins (TC, LDL-C, HDL-C, TG, ApoB, ApoA1)Change in HbA1cChange in eGFRChange in smoking statusChange in mean number of cigarettes smoked per dayChange in SCI scoreChange in ISI scoreChange in PSQI scoreChange in SOLChange in WASOChange in total sleep timeChange in sleep efficiencyChange in proportion of participants with SE ≥85% at 8 weeksChange in proportion of participants with SOL ≤30 minutes at 8 weeksChange in proportion of participants with PSQI <5 at 8 weeksChange in proportion of participants with SCI score ≤5.9 at 8 weeksChange in proportion of participants with ISI score ≥15 at 8 weeksChange in BDI scoreChange in BAI score

#### Cointerventions

Participants in this trial will ideally not receive any antihypertensive medications throughout the 8-week period. However, participants receiving up to two antihypertensive agents at the time of entry into the trial are eligible for inclusion, provided that no recent (within the previous 8 weeks) changes occurred in type or dose of antihypertensive medications and there are no planned change to antihypertensive medication over the next 8 weeks (during the trial). Note: in patients with mild hypertension and no history of CVD, current guidelines recommend an initial period of lifestyle intervention, consistent with our approach. Treating clinicians will be permitted to use clinical judgment in initiating and dose-adjusting antihypertensive therapies for both study groups during the 8-week trial, where appropriate. Participants who are stable on cardiovascular preventive therapies (no change in previous 3 months), such as lipid-lowering agents, antithrombotic therapies, oral hypoglycemic agents, and insulin will continue their usual treatment. Participants not taking these agents will be encouraged to avoid initiation of treatment with these agents, until the 8-week trial period has been completed. However, treating clinicians will be permitted to use usual clinical judgment in initiating and dose-adjusting such medications, where appropriate. Initiation and/or dose adjusting of cointerventions will be recorded and measured and accounted for using sensitivity analysis. Participant adherence to the intervention will also be measured, and adjusted for using sensitivity analysis. For example, we will analyze the data for evidence of a dose/response relation between degree of reduction in SBP and number of online sleep sessions completed.

### Sample-size calculation

The primary outcome is the mean difference in SBP reduction over the 8-week period between the two study groups. Our estimated minimum clinically meaningful effect size is 5 mm Hg, with an estimated standard deviation (SD) for SBP reduction of 8.3 mm Hg in the intervention group and 7.7 mm Hg in the control group, based on previous research
[31]. The minimum effect size is based on previous randomized controlled trials reporting a reduction in CVD with reductions in SBP of 5 mm Hg or greater, and the reduction in blood pressure with lifestyle interventions observed in previous trials
[31–33]. A 5.6-mm Hg reduction in blood pressure in the ADVANCE trial resulted in relative-risk reductions of 9% for major vascular events, and 18% for cardiovascular death
[34]. Based on a two-sample comparison of means at a significance level of α = 0.05 and power of 80% to detect a difference of 4 mm Hg (power of 90% to detect a difference of 5 mm Hg) between treatment arms, and an estimated 5% loss to follow-up, a per-group sample size of 67 participants will be required.

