### Statistical analysis plan

#### Descriptive statistics and baseline characteristics

Descriptive statistics will be used to describe the baseline characteristics of the study sample, the flow of trial participants, and the level of missing data for both predictor and outcome variables. All losses to follow-up and dropouts will be counted, and where possible, reasons documented. Categoric variables will be described by using frequencies and percentages. Histograms and boxplots will be used to evaluate the distribution of continuous variables and to identify any outliers or potential errors in the data, with follow-up verification if necessary from the case-report forms. For continuous variables, the mean and standard deviation will be used to describe the typical value and spread in the sample. For continuous variables that are not normally distributed, the median and interquartile range will be used to describe the typical value and spread in the sample. All tests of significance will be two-sided and conducted at an α = 0.05 for level of statistical significance.

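### The sample-size section states 90% power at 5 mm Hg, but its own inputs give about 94%; the size of 67 per group is correct and only the parenthetical needs changing

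*Protocol article*

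**What the plan says.** All the inputs are in the protocol article, and all but one are under Sample-size calculation.

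- Target: "Our estimated minimum clinically meaningful effect size is 5 mm Hg".
- Variability: assumed standard deviations for "SBP reduction of 8.3 mm Hg in the intervention group and 7.7 mm Hg in the control group".
- Test: "Based on a two-sample comparison of means at a significance level of α = 0.05". The section on descriptive statistics and baseline characteristics supplies the sidedness: "All tests of significance will be two-sided and conducted at an α = 0.05 for level of statistical significance".
- Power: "power of 80% to detect a difference of 4 mm Hg", followed in parentheses by "power of 90% to detect a difference of 5 mm Hg".
- Attrition: "an estimated 5% loss to follow-up".
- Result: "a per-group sample size of 67 participants will be required".

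The two power figures stand side by side in one sentence about one design. Neither is qualified as a minimum or as approximate.

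**The concern.** A design has one power curve. Once its power at 4 mm Hg is fixed, its power at 5 mm Hg follows. Moving from 4 to 5 mm Hg is a 25% larger difference, whereas going from 80% to 90% power takes a difference only about 16% larger. The two printed figures therefore cannot both be exact.

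The figure in doubt is the only power quoted at the difference the trial itself calls the smallest worth detecting. It tells a reader how often the trial would miss such an effect: 10% of the time if the printed figure is right, about 6% if the inputs are. That has some bearing on how a null result in a proof-of-principle trial is described, although the confidence interval for the treatment difference would carry most of that judgement.

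**Working it through.** **Inputs.** SDs 8.3 and 7.7, α = 0.05, 67 per group and 5% loss, from Sample-size calculation; two-sided testing, from the section on descriptive statistics. Normal quantiles: 1.960 (two-sided 0.05), 0.842 (80% power), 1.282 (90% power). Evaluable per group: 67 × 0.95 = 63.65, so 63 to 64.

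**Step 1: reproduce the stated size.**

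n per group = (SD₁² + SD₂²) × (z for α + z for power)² / difference²

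- 8.3² + 7.7² = 68.89 + 59.29 = 128.18 (root-mean-square SD 8.006).
- 4 mm Hg at 80%: 128.18 × 2.802² / 16 = 62.88, rounded up to 63. Allowing for loss, 63 / 0.95 = 66.3, rounded up to **67**, as printed.

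**Step 2: power of that design at each difference.**

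SE = √(128.18 / n); power = Φ(difference / SE − 1.960)

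- n = 63: SE = 1.426. At 4 mm Hg, Φ(2.804 − 1.960) = 80.1%, as printed. At 5 mm Hg, Φ(3.505 − 1.960) = 93.9%, against a printed 90%.

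| Evaluable per group | 4 mm Hg, normal | 4 mm Hg, t | 5 mm Hg, normal | 5 mm Hg, t |
|---|---|---|---|---|
| 63 | 80.1% | 79.5% | 93.9% | 93.6% |
| 64 | 80.7% | 80.1% | 94.2% | 93.9% |
| 67 (no loss) | 82.4% | 81.9% | 95.1% | 94.8% |

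**Step 3: where 90% is reached.** Difference = (1.960 + 1.282) × SE. This is 4.62 mm Hg with 63 evaluable and 4.59 mm Hg with 64, so about 4.6 mm Hg.

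**Step 4: what 90% at 5 mm Hg alone would need.** 128.18 × 3.242² / 25 = 53.87, rounded up to 54 evaluable; 54 / 0.95 = 56.8, so 57 randomised per group (55 and 58 by the t calculation).

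**Step 5: could a different SD or group size reconcile the pair?** No. In the normal approximation, 80% power at 4 mm Hg means 4/SE = 2.802. Then 5/SE = 2.802 × 1.25 = 3.502, and the power is Φ(3.502 − 1.960) = 93.8%. SD, group size and attrition enter only through SE, which the first statement has already fixed. One-sided testing does not help either: 4/SE = 1.645 + 0.842 = 2.487, 5/SE = 3.108, and Φ(3.108 − 1.645) is about 93%.

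The reverse also fails. If 90% at 5 mm Hg were exact, power at 4 mm Hg would be Φ(3.242 × 0.8 − 1.960) = Φ(0.633), about 74%. Among the variants tried at the planned number evaluable, the closest to 90% uses 8.3 as a common SD, with the t calculation and 63 evaluable. It gives 91.9% at 5 mm Hg but lowers power at 4 mm Hg to 76.5%.

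**The case against.** The strongest defence is that both figures are requirements. Power of 80% at 4 mm Hg needs 67 per group, 90% at 5 mm Hg needs 57 or 58, and the larger number meets both. Read as at least 90%, the parenthetical is true. The part of this that stands is important: 67 satisfies both conditions, and nobody is led to think the trial stronger than it is. But the text does not say at least. The two figures are given in parallel, and the first matches its inputs exactly, so a reader will take the second in the same way.

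It is also fair to say that both figures are nominal. They describe an unadjusted two-sample comparison with assumed SDs, whereas the Statistical analysis section specifies a linear mixed model with covariates. This limits how much the 4 points matter in practice. It does not make 90% the right answer to the calculation the protocol describes.

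A reader might be tempted to infer more, and the document does not support it:

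- *That 67 is wrongly derived or does not match its stated reason.* It follows exactly from 80% power at 4 mm Hg with 5% loss.
- *That sizing on 4 mm Hg while naming 5 mm Hg as the smallest meaningful effect is a mistake.* It is a cautious choice, stated openly in the section, and it gives more than 90% power at the declared target.
- *That about 10 participants per group (67 against 57) are surplus.* The 4 mm Hg condition requires them.

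**Conclusion.** The printed 90% at 5 mm Hg is a misstated power. On the protocol's own inputs the figure is about 94% (93.6% to 94.2% across 63 or 64 evaluable per group and normal or t calculation), so it is understated by about 4 percentage points. The difference detectable with 90% power is about 4.6 mm Hg.

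The conclusion assumes the stated SDs, two-sided α of 0.05, the stated 5% loss and the two-sample comparison that the section names. The inconsistency between the two power figures does not depend on the SDs or the attrition rate.

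The point is minor. The error is conservative, the sample size is correct, and the trial is not underpowered at its declared target.

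**What to change.** In the sample-size section, change the parenthetical to say that power is about 94% at a difference of 5 mm Hg. If the authors prefer to keep a 90% figure, they can attach it to a difference of about 4.6 mm Hg. The cost is one phrase; the sample size, the 4 mm Hg statement, enrolment and the analysis stay as they are.

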### Statistical analysis plan

#### Descriptive statistics and baseline characteristics

Descriptive statistics will be used to describe the baseline characteristics of the study sample, the flow of trial participants, and the level of missing data for both predictor and outcome variables. All losses to follow-up and dropouts will be counted, and where possible, reasons documented. Categoric variables will be described by using frequencies and percentages. Histograms and boxplots will be used to evaluate the distribution of continuous variables and to identify any outliers or potential errors in the data, with follow-up verification if necessary from the case-report forms. For continuous variables, the mean and standard deviation will be used to describe the typical value and spread in the sample. For continuous variables that are not normally distributed, the median and interquartile range will be used to describe the typical value and spread in the sample. All tests of significance will be two-sided and conducted at an α = 0.05 for level of statistical significance.

#### Statistical analysis

The primary analysis will use the on-treatment dataset for all outcomes. On-treatment is defined as those participants who completed at least one session of the online sleep intervention. A secondary analysis will use the intention-to-treat dataset, and a third, per-protocol analysis, will also be carried out for all outcomes, with postrandomization exclusions due to ineligibility, noncompliance, loss to follow–up, or missing data.

A linear mixed model will be used to compare changes in mean 24-hour ambulatory SBP (and other secondary outcomes) from baseline to 8 weeks after randomization. We will adjust for covariates associated with the intervention and the outcome as appropriate (for example, age, baseline SBP, baseline DBP, baseline SCI score). The selection of explanatory variables for inclusion in the final model will be based on clinical plausibility and variable selection routines, the LASSO, and regression trees. It will be assumed that missing data are missing at random and therefore accounted for in the mixed model. The validity of this assumption will be investigated by looking at the missing data patterns and by modeling the probability of missing data based on the explanatory variables available. The sensitivity of the missing value-generating mechanism to the choice of variables for inclusion and the final conclusions will be assessed by using multiple imputations via chained equations and predictive mean matching. Model checking will be performed by using suitable model diagnostics and residual plots. All statistical analyses will be performed by using the software packages SPSS version 21.0, R version 2.15.3 and Minitab version 16.2.

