**Methods:**

*Trial design:* Randomized-controlled, two-group, parallel, blinded, single-center, Phase II trial of 134 participants. *Population and recruitment*: Primary prevention population of participants with hypertension (systolic blood pressure, 130 to 160 mm Hg; diastolic blood pressure, <110 mm Hg) and poor sleep quality in a community setting. *Intervention:* Multicomponent online sleep intervention consisting of sleep information, sleep hygiene education, and cognitive behavioral therapy. *Comparator:* Standardized cardiovascular risk factor and lifestyle-education session (usual care). *Primary outcome:* Change in mean 24-hour ambulatory systolic blood pressure between baseline and 8-week follow-up. Hypertension has been selected as the primary outcome measure because of its robust association with both poor sleep quality and cardiovascular disease. *Statistical analyses*: Intention-to-treat analysis by using a linear mixed model.

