## Methods

### Trial design

Randomized, two-group, parallel, blinded, controlled, single-center trial. This is a Phase II, efficacy, proof-of-principle trial with an allocation ratio of 1:1.

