### Randomization

A randomization strategy using randomly permuted blocks of varying block size is being used, which allows the assignment schedule to be preplanned before participant recruitment. The randomization schedule is constructed by using a computer-generated list of pseudo-random numbers. A centrally administered, computer-generated randomization scheme is being used to assign individual participants randomly in a 1:1 ratio, to either the intervention or control groups. Once a participant is deemed eligible for trial entry and has provided written informed consent, a researcher assigns a unique study-identification number to the participant and contacts the online sleep intervention (Sleepio) team with the participant's name, their assigned participant number, and contact details (Email address and telephone number). The Sleepio team then assigns the participant to the next available randomization number on the list, corresponding to a particular treatment assignment (Sleepio intervention or control). Participants randomized to Sleepio receive a code via Email to access the online sleep intervention. The Sleepio team holds the central record of all participants who have been randomized, along with the corresponding randomization numbers and treatment-group assignments. All investigators at the HRB-CRFG, including the statistician, are blinded to participant treatment-group assignment. At the end of the trial, treatment assignments will be compared with the randomization list, to detect any incorrect assignments, and following completion of statistical analyses, all investigators and trial personnel will be unblinded.

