### Study interventions

#### Components of the sleep intervention

The sleep intervention (Sleepio) is a multicomponent online intervention consisting of sleep information and sleep-hygiene education, along with behavioral and cognitive components. This intervention was developed after consultation with a sleep psychologist. It is based on three previous randomized controlled trials investigating the efficacy of an intervention to improve sleep in participants with insomnia, one of which was an online cognitive behavioral therapy intervention for chronic insomnia disorder
[25]. The interventions were similar, with two of the trials showing a significant improvement in sleep efficiency
[23, 25], and the third showing a significant improvement in sleep latency, wakefulness after sleep onset, and sleep efficiency (measures of sleep quality), as well as improvements in mental health and energy
[24].

Participants in the sleep-intervention arm also receive ”usual” care (standardized cardiovascular risk-factor education program), similar to participants in the control arm. Thus, the comparison is: standardized cardiovascular education + online sleep intervention versus standardized cardiovascular education.

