#### Subgroup and sensitivity analyses

The primary outcome will be analyzed by subgroups based onAge (≥65 years versus <65 years)SexSeverity of hypertension at baseline (SBP 130 to 150 versus 151 to 160)Use of antihypertensive medication at time of entry into the trialIntroduction of antihypertensive medication during the trialSleep condition indicator score ≤5.9 versus >6.0Body mass index (BMI ≤25 versus >25)Employment statusConcomitant use of hypnoticsDepression, score ≥17 versus <17 on BDIAnxiety, score ≥22 versus <22 on BAIAdherence to the intervention

Statistical tests of interaction will be performed for all subgroup analyses. A sensitivity analysis will be performed to assess the influence of adherence to the intervention, on the estimated treatment effect. These analyses will use the on-treatment dataset.

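### The primary analysis set is defined by starting the online sleep course, which only the intervention arm can do, and it contradicts the intention-to-treat analysis announced in the abstract

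*Protocol article*

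**What the plan says.** The abstract, under Methods, gives the analysis in one line: "Intention-to-treat analysis by using a linear mixed model". It names no other analysis set.

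The Statistical analysis section sets a different order. "The primary analysis will use the on-treatment dataset for all outcomes", and "On-treatment is defined as those participants who completed at least one session of the online sleep intervention". ITT follows in second place: "A secondary analysis will use the intention-to-treat dataset, and a third, per-protocol analysis, will also be carried out for all outcomes".

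The Subgroup and sensitivity analyses section carries the same set forward: "These analyses will use the on-treatment dataset".

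Only one arm can meet the definition. Under Randomization, "Participants randomized to Sleepio receive a code via Email to access the online sleep intervention". The comparison, under Components of the sleep intervention, is "standardized cardiovascular education + online sleep intervention versus standardized cardiovascular education". Components of the control intervention lists risk-factor and lifestyle education only. Nowhere does the article say how a control participant enters the on-treatment set.

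**The concern.** A primary analysis set should be one that both arms enter on the same terms, preferably at randomization. Here entry depends on a behavior that occurs after randomization and is possible in one arm only. People who never open the course are likely to differ from those who do, in motivation and in how far they follow the lifestyle advice that both arms receive. Removing them from one arm and keeping their counterparts in the other gives up the protection of randomization, most plausibly in favor of the intervention.

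Three features add to the stakes. The Discussion (Methods of minimizing bias) makes a significant effect the condition for a phase III trial. The same section already accepts a possible attention bias because there is no attention placebo, and selecting engaged participants in one arm would add to it. And because the abstract and the Methods name different primary sets, a reader cannot tell which result the trial stands on.

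**Working it through.** **1. The two readings of the definition**

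- *Literal:* the set is those with at least one completed sleep session. Controls have no access code, so 0 of the 67 planned controls qualify and no between-arm comparison exists.
- *Charitable:* all controls are kept, and intervention participants with no session are removed. The exclusion is one-sided.

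No other section supplies a rule that avoids both.

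**2. The article's own sample size**

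Inputs from Sample-size calculation: SDs of 8.3 and 7.7 mm Hg, differences of 4 mm Hg (80% power) and 5 mm Hg (90% power), 5% loss to follow-up. Alpha is 0.05, two-sided.

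- Pooled SD = √[(8.3² + 7.7²)/2] = 8.006.
- For 4 mm Hg: n = 2 × 8.006² × (1.960 + 0.842)² / 4² = 62.9, so 63 per arm; 63/0.95 = 66.3, so **67**. The stated figure reproduces.
- For 5 mm Hg at 90% power: 54 per arm; 54/0.95 = 56.8, so 57. The stated 67 is enough.

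The calculation allows for 5% loss to follow-up and nothing for excluded non-starters. It fits an analysis of the arms as randomized.

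**3. Bias under the charitable reading**

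Let *s* be the share of the intervention arm that starts, and *D* the SBP reduction in starters minus that in non-starters when nobody is treated. If the course has no effect, the retained intervention group has the starters' mean, while the control group has the mix of both types. The expected difference is therefore

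bias = (1 − *s*) × *D*.

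Evaluable numbers: 67 × 0.95 = 63.65 controls and 63.65 × *s* in the intervention arm. Then

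SE = √[8.3²/(63.65 *s*) + 7.7²/63.65]

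and

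type I error = Φ(−1.96 + bias/SE) + Φ(−1.96 − bias/SE).

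The article gives neither *s* nor *D*; all values below are assumptions.

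| *s* | SE | *D* = 2 | *D* = 4 | *D* = 6 | *D* = 8 |
|---|---|---|---|---|---|
| 0.95 | 1.44 | 0.1 mm Hg; 0.051 | 0.2; 0.052 | 0.3; 0.055 | 0.4; 0.059 |
| 0.85 | 1.49 | 0.3; 0.055 | 0.6; 0.069 | 0.9; 0.093 | 1.2; 0.128 |
| 0.70 | 1.57 | 0.6; 0.067 | 1.2; 0.119 | 1.8; 0.208 | 2.4; 0.332 |

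(Each cell: bias in mm Hg; two-sided type I error.)

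Worked example, *s* = 0.85 and *D* = 4: bias = 0.15 × 4 = 0.6; SE = √(68.89/54.1 + 59.29/63.65) = 1.485; 0.6/1.485 = 0.404; Φ(−1.556) + Φ(−2.364) = 0.069.

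**4. Power**

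- *On-treatment set, s = 0.85:* power for 4 mm Hg falls from 80.5% to about 77% through lost participants alone.
- *ITT, if 4 mm Hg is the ITT difference:* power stays at 80.5% with 63.65 evaluable per arm.
- *ITT, if 4 mm Hg is the effect in starters and non-starters gain nothing (assumption):* the ITT difference is 4*s*. Power is 76%, 72% and 67% at *s* = 0.95, 0.90 and 0.85, and 80% power would need 74, 83 and 93 per group.
- *ITT, if the effect in starters is 5 mm Hg:* power at 67 per group is 92%, 89% and 85% for the same *s*.

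**The case against.** The strongest case on the other side accepts the conflicting text and questions its size and consequences.

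- *The inputs may be too pessimistic.* The adherence target of more than 85% is not defined as completing one session. One session out of six is a low bar, so 15% non-starters is nearer a ceiling, and 30% has no basis in the article. A *D* of 4 to 8 mm Hg is half to one SD of purely prognostic difference. With *D* = 2 and at most 15% non-starters, the type I error stays at or below 5.5%. If non-starters are often also lost to follow-up, the on-treatment and ITT results move closer. All of this stands, so the figures are illustrations.
- *The empty control arm is a drafting gap.* The aims and the sample-size section plainly intend two groups. That is fair, but the natural repair is the one-sided exclusion.
- *The Methods rank the three sets, and ITT is prespecified for every outcome.* This limits the room for choosing after the data are seen. It does not remove the conflict with the abstract, and it places the biased contrast first.
- *The phase III sentence names no dataset, and the direction of bias is not proven.* Both are correct. The direction is plausible on the article's own reasoning, since the Discussion describes motivated, adherent volunteers as the people likely to benefit.
- *Session data are legitimate for an adherence analysis.* That holds for the dose-response analysis within the intervention arm, described under Cointerventions. It does not hold for treatment-by-subgroup comparisons.

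A proof-of-concept aim is a reason to want the effect in starters. It is not a reason to estimate it by dropping people from one arm.

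**Conclusion.** The plan is wrong as written and has to be corrected before the analysis. Two conclusions need no assumption: the abstract and the Methods name different primary analyses, and the set that the Methods make primary can be entered by one arm only. An unseen analysis plan would not undo either statement.

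The numerical effect does depend on assumptions. It ranges from negligible (0.1 mm Hg and 5.1% type I error with 5% non-starters and *D* = 2) to material (1.2 mm Hg, or 30% of the 4 mm Hg target, and 12.8% with 15% non-starters and *D* = 8). The 30% non-starter row only shows how the error grows.

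There is also a practical conflict. The Randomization and Blinding sections keep the statistician blinded until the analyses are complete, yet a set built from session completion reveals the arm of everyone with a recorded session.

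**What to change.** - **Statistical analysis:** make ITT primary for all outcomes, meaning all randomized participants, analyzed as assigned, whatever number of sessions they completed. This agrees with the abstract.
- **Subgroup and sensitivity analyses:** run the subgroup comparisons on the same ITT set. Limit session-based dose-response work to the intervention arm and label it as such.
- **On-treatment and per-protocol analyses:** keep them as supportive, and state how controls enter each set.
- **Effect in starters, if wanted:** estimate a complier-average causal effect with randomization as the instrument. State its assumptions: assignment does nothing for those who never start, and controls do not obtain the course.
- **Sample-size calculation:** say whether the 4 to 5 mm Hg is the difference between arms as randomized or the effect in starters.

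The cost is mostly wording, and no new data are needed. If 4 to 5 mm Hg is the ITT difference, 67 per group stands. If it is the effect in starters, ITT dilutes it: at 85% starters, power with 67 per group is about 67% for 4 mm Hg and 85% for 5 mm Hg. The sponsor should then either accept that power openly or revisit the target of 134.
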